### Analysis plan

### Analysis of primary outcome

In the South African and western Kenyan sites, we will analyze population level change in directly-observed HIV incidence over time, with all data available from the HDSS sero-surveys, making comparisons among three calendar time periods as follows:Pre-DREAMS roll-out: the 5–10 years prior to DREAMS (up to and including 2015 in South Africa and 2016 in Gem, Kenya [see ‘Sample Sizes’ below for details])During early DREAMS implementation: 2016Post-DREAMS: 2017–2019 (rolled out)

Our main comparison will be between the post-DREAMS time period, and the two earlier time periods.

In Zimbabwe, we will compare HIV incidence between sites where DREAMS+PrEP has and has not been implemented, over two years of follow-up. In the absence of randomization, the analysis will adjust for known individual-level determinants of HIV incidence.

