### The DREAMS core package

The DREAMS Partnership supports a core package of interventions targeted at AGYW, their families, wider communities, and men characterized to be the sexual partners of AGYW [7]. The package is comprised of evidence-based interventions shown to address HIV risk behaviours, HIV transmission, socio-economic vulnerabilities and gender-based violence (Table 1).

**Table 1 Tab1:** Interventions and target populations of the DREAMS Core Package

Target population and strategy	Evidence-based intervention
*Individual interventions (delivered directly to adolescent girls and young women)*	
Empower girls and young women and reduce their risk	▪ Condom promotion and provision ▪ HIV testing and counselling services (HTS) ▪ Oral pre-exposure prophylaxis (PrEP) for HIV, offered to a subset of females at exceptionally high risk and in select countries ▪ Post-violence care ▪ Expanded contraceptive method mix ▪ Social asset building
*Contextual interventions (not all delivered directly to adolescent girls and young women but from which they can benefit)*	
Mobilize and strengthen the community for change	▪ School-based HIV and violence prevention for boys and girls ▪ Community-based HIV and violence prevention for boys/young men and girls/young women ▪ Community mobilization and norms change for community leaders, boys and men
Strengthen families	▪ Parenting and caregiver programmes for vulnerable adolescent girls ▪ Social protection (cash transfers, educational subsidy, combination socioeconomic approaches)
Decrease risk in sexual partners of AGYW	▪ Characterisation of male partners to target highly effective interventions, e.g., HIV testing services, antiretroviral therapy (ART) and voluntary medical male circumcision (VMMC)

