#### uMkhanyakude, KwaZulu-Natal, South Africa

The Africa Health Research Institute (AHRI; formerly the Africa Centre for Population Health) in uMkhanyakude, KwaZulu-Natal, has followed a total of ~ 160,000 individuals from 11,000 geocoded households from 2000, in a 428 km^2^ surveillance area. Demographic surveys have been conducted three times a year, with annual collection of individual socio-economic, behavioral, and HIV service uptake data alongside collection of dried blood spots for laboratory testing for HIV infection. AHRI has a memorandum of understanding with the Department of Health that enables linkage of the population surveillance data to the primary care electronic record systems in the local health care facilities (2010 onwards) and to the TIER.Net electronic record system for HIV treatment (2004 onwards), as well as to all clinical laboratory test results of patients in the sub-district through linkage with the National Health Laboratory Systems (NHLS) database (since 2004). Since 2017, AHRI has embedded clinical research assistants in all primary health care settings in the surveillance area. They electronically capture details on the reason for attendance, and these clinic attendance data are linked to the demographic surveillance data.

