### Measurement and analysis of key variables

For component 1, the population-based surveillance in the general population of AGYW and men, the primary comparison is across three time periods: pre-DREAMS, during the early roll-out of DREAMS interventions, and post-DREAMS. The aim is to know whether HIV incidence among AGYW aged 15–24 years (the primary outcome, directly observed through repeat testing) and key secondary outcomes, measured among both AGYW and men, have changed over time at population-level. The primary and secondary outcomes are summarized in Table 2, with secondary outcomes lying on the three pathways of central interest that are between the interventions and HIV incidence: social, behavioural (sexual), and biological protection. The extent to which any changes can be attributed to DREAMS interventions will be assessed in the context of other secular changes, and the findings of the process evaluation. For example, given the background scale-up of universal testing and treatment for HIV, our findings on HIV incidence trends among AGYW will be placed in the context of trends in HIV incidence and the uptake of HIV testing and treatment among those who are not directly targeted for DREAMS HIV prevention interventions.

**Table 2 Tab2:** Primary and secondary measures of impact at the population-level in the South African and Kenyan evaluation sites, to be estimated by comparing calendar time periods that represent pre-DREAMS, during early roll-out of DREAMS, and after DREAMS roll-out

	Adolescent girls and young women		Male sexual partners
	15–19 years	20–24 years	(15–34 years)
Primary Outcome	HIV incidence^a^		HIV incidence^a^
Secondary Outcomes			
*Biological protection*	Knows HIV status^b^		
	HIV/STI prevalence	STI prevalence & Incidence	Uptake of VMMC
			Use of ART
			Community HIV viral load^d^
*Behavioral protection*	Ever had sex		Number of sexual partners (in last year / lifetime)
	Age at first sex		
	Number of sexual partners (in last year / lifetime)		
	Age-disparity with sexual partners		
	Ever been pregnant	Unmet need for contraception^c^	Concurrency of sexual partners
	Age at first / subsequent pregnancies		
	Use of condoms^e^ Any condomless sex		
	Transactional sex		
*Social protection*	In or completed school	In employment or completed vocational / microfinance training	Gender norms: support gender equity
	Age at first marriage		Experience of violence (exposure to / victimization / perpetration)
	Experience of violence		

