^a^not collected in Nairobi

^b^know they are HIV+ or have tested HIV negative in the past 12 months

^c^ do not want a child in next 2 years or ever but not using a method to prevent pregnancy

^d^ uMkhanyakude only

^e^ Used condom at last sex (in past 12 months); Any condomless sex in last 1 month / last 12 months and in the last 3 months

For component 2, the nested cohorts of AGYW designed to measure pathways of change, the primary exposure is uptake of DREAMS interventions among individual AGYW, considering single components as well as the number and combination of components of the core package that were received. The extent to which AGYW are aware of, invited into, and participate in DREAMS interventions will be summarized, using the core package and primary/secondary interventions as frameworks to categorise interventions and standardize across the settings. (See Table 3 for proposed, a priori measures of DREAMS uptake.) Comparisons of mediators and secondary outcomes will then be made among AGYW according to their uptake of DREAMS interventions.

**Table 3 Tab3:** Outcomes, mediators of change in the outcomes, and uptake of DREAMS interventions, to be captured via nested DREAMS cohorts of adolescent girls and young women (in Kenya and South Africa) and young women who sell sex (in Zimbabwe)

	AGYW (South Africa and Kenya)		YWSS (Zimbabwe)
	13–17 years^b^	18–22 years^b^	18–24 years
Primary	n/a ^a^		HIV incidence
Secondary Outcomes	Knows HIV status		
	Number of lifetime pregnancies		
	Reduced experience of violence		
	Incidence & prevalence of HSV-2/other STI		HIV prevalence
	Aware of partners’ HIV status		Number of sexual partners
			Engaged in transactional sex for economic reasons
	Age at first sex	Number of sexual partners in the last 12 months	Use of condoms & PrEP with regular/transactional sex partners
	Age at first /subsequent pregnancies	Age at first / subsequent pregnancies	Adherence to HIV treatment and care services
	Condom use		Reduced food insecurity
	Unmet need for contraception		
	Age-disparity with sexual partners	HIV risk of sexual partners (to be defined a priori)	
	No/less transactional sex		
	Stay in school	In employment or completed vocational / microfinance training	
	Age at first marriage or first long-term/live-in partner		

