#### Sample sizes

HIV incidence - the primary endpoint for the impact evaluation - will be measured using HDSS data in uMkhanyakude and Gem, and data from the cohorts of young women who sell sex in Zimbabwe. In uMkhanyakude, HIV incidence was ~ 6 per 100 person-years among AGYW aged 15–24 years old during 2011–2015, and ~ 4.6 and ~ 7.5 per 100 person-years among those aged 15–19 and 20–24 years respectively, based on a total of 7687 person-years of follow-up. Assuming, conservatively, that there will be ~ 3000 person-years of follow-up during 2017–2019 (40% of 7687), [20] then study power is > 90% to show an overall reduction in HIV incidence of 30, and > 90% in sub-group analysis of AGYW aged 15–19 and 20–24 years to show a 40% reduction in HIV incidence (Fig. 3a). In Gem, western Kenya, HIV incidence was ~ 0.7 per 100 person-years among AGYW aged 15–24 years during 2011–2016, based on a total of 8236 person-years of follow-up [21]. (Whereas sero-surveys are conducted annually in uMkhanyakude, they are less frequent in Gem: data are available from three sero-surveys in Gem between 2011 and 2016. Sero-conversions observed during this period, including those estimated from the 2016 survey, will be considered ‘pre-DREAMS’ because they are unlikely to be influenced by DREAMS by this early stage of implementation.) During 2017–2019, all AGYW in Gem will be sought for participation in the HDSS; with a participation rate of 70% in each year, and an annual out-migration rate of 20%, it is estimated that there will be ~ 9000 person-years of follow-up during 2016–2019. Study power is low to show a change in HIV incidence in sub-group analyses of AGYW aged 15–19 and 20–24 years, but ~ 80% to show an overall reduction of 45, and 90% to show an overall reduction of 50% in HIV incidence (Fig. 3b).

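### Incidence is counted from repeat survey tests alone; if women diagnosed between rounds re-test less as testing expands, part of an observed decline could be spurious, and uMkhanyakude's linked records allow a check

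*Protocol article*

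**What the plan says.** The section on measurement and analysis of key variables defines incidence among women aged 15–24 as "the primary outcome, directly observed through repeat testing". The section on analysis of the primary outcome names the data source: "we will analyze population level change in directly-observed HIV incidence over time, with all data available from the HDSS sero-surveys". It then sets the contrast: "Our main comparison will be between the post-DREAMS time period, and the two earlier time periods".

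Three other statements bear on this:

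- The core package in Table 1 includes "HIV testing and counselling services (HTS".
- The measurement section asks for incidence trends to be read in context, "given the background scale-up of universal testing and treatment for HIV".
- Knowledge of HIV status is a secondary outcome over the same periods. The footnote to Table 2 defines it as women who "know they are HIV+ or have tested HIV negative in the past 12 months".

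The uMkhanyakude setting section describes linkage of surveillance data "to the TIER.Net electronic record system for HIV treatment (2004 onwards", and to clinical laboratory results from the same year. The study design section says that linkage to HIV clinic data is possible in both incidence sites. Nowhere is linkage assigned a role in detecting seroconversions or in describing who is re-tested.

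**The concern.** Under the stated rule, a new infection counts only if the woman gives a further survey sample. If diagnosed women return for survey testing less often than undiagnosed women, some infections are missed. Constant under-capture would cancel in a rate ratio. The problem arises if the diagnosed share, or diagnosed women's participation, changes between the periods compared. The programme and the background scale-up are both meant to raise the diagnosed share.

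Any resulting bias would look like a programme effect and would grow as testing succeeds. Historical trend data would not remove it, because the change coincides with roll-out.

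**Working it through.** **The plan's own figures.** Take two Poisson rates at two-sided alpha 0.05 (assumed; the article does not state it). For uMkhanyakude, events before are 0.06 × 7687 = 461. Events after a 30% reduction are 0.042 × 3000 = 126. The standard error of the log rate ratio is √(1/461 + 1/126) = 0.1005. The test statistic is 0.357/0.1005 = 3.55, giving power of about 94%, which agrees with the stated figure of over 90%. For Gem (0.7 per 100, 8236 and 9000 person-years), a 45% reduction gives 79–80% depending on the variant, against about 80% stated. The power figures are not in dispute.

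**Inputs for the bias, all assumed.**

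- d₀ and d₁: share of seroconverters diagnosed before their next survey test, in the earlier and later period.
- r: probability that a diagnosed seroconverter ever gives a later survey sample, relative to an undiagnosed one.

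**Formula.** The relative share of seroconversions observed is 1 − d(1 − r). With no true change, and person-time taken as unaffected, the apparent rate ratio is [1 − d₁(1 − r)] / [1 − d₀(1 − r)].

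| d₀ → d₁ | r | Apparent rate ratio | Spurious decline |
|---|---|---|---|
| 0.3 → 0.4 | 0.8 | 0.92/0.94 = 0.979 | 2.1% |
| 0.2 → 0.4 | 0.8 | 0.92/0.96 = 0.958 | 4.2% |
| 0.2 → 0.5 | 0.6 | 0.80/0.92 = 0.870 | 13.0% |
| 0.3 → 0.6 | 0.6 | 0.76/0.88 = 0.864 | 13.6% |
| 0.2 → 0.6 | 0.5 | 0.70/0.90 = 0.778 | 22.2% |
| any | 1 | 1.000 | 0% |

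With d₀ in 0.2–0.3, d₁ in 0.4–0.6 and r in 0.5–0.8, the first and fifth rows are the extremes.

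**Consequence in uMkhanyakude.** The chance of a significant decline with no true change is nominally 2.5% in that direction. It becomes about 7% at a rate ratio of 0.958, 33% at 0.870 and 74% at 0.778. At 0.870, a true 30% reduction would appear as 1 − 0.7 × 0.870 = 39%.

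**An offset.** Suppose negative women tested in clinics also re-test less: 30% then 60% of them tested, with relative participation 0.8. Their person-time is then scaled by 0.94 and 0.88. The 13.6% row becomes (0.76/0.88)/(0.88/0.94) = 0.92, a decline of about 8%. If the effect is equally strong in negative women, the bias cancels.

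**Can weighting help?** In a simulation at 6 per 100 person-years with d 0.3 → 0.6 and r 0.6, observed incidence was 5.29 then 4.58. Inverse-probability weights restored 5.99 in both periods. Those weights were the true ones, so this is a best case.

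**The case against.** The strongest reply is that the key premise has no support in the article. Nothing says that diagnosed women give fewer survey samples. In uMkhanyakude the sample is a dried blood spot for laboratory testing and is not presented as a way to learn one's status. This stands: the size of the bias is conditional and may be nil.

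Second, this is a condensed article with site protocols available on request, and no sentence excludes linked diagnoses. That is fair as regards weighting details. But the article does fix how the primary outcome is ascertained, and the proposal is a check on that choice rather than a request for missing text.

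Third, checks already exist: comparison with new antenatal diagnoses, trends in groups not directly targeted, and small-area dose-response. They are useful context, but none recovers missed seroconverters, and untargeted groups face the same testing scale-up.

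Two stronger readings are tempting and not supported:

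- A reader might take the fall in yearly person-years, from 7687/5 = 1537 to 3000/3 = 1000 (65%), as evidence of falling re-testing. The article's words are "Assuming, conservatively, that there will be ~ 3000 person-years of follow-up during 2017–2019 (40% of 7687": a cautious sizing value. A general fall in re-testing does not bias a rate, and the ratio does not enter the formula.
- A reader might infer that the bias favours DREAMS in both sites. In Gem, three sero-surveys in 2011–2016 give way to participation assumed in each year of 2017–2019. Shorter intervals leave less time for diagnosis before the next round, so the diagnosed share could fall.

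Finally, a woman who skips one round may be detected at a later one, which weakens the bias except near the end of 2017–2019.

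**Conclusion.** The point holds as a conditional weakness of the stated ascertainment rule. It is not a demonstrated bias. In uMkhanyakude, under the assumed ranges, survey-only detection would produce a spurious decline of about 2% to 22% with no true change. The decline is smaller with offsetting behaviour among negative women or with later detection, and zero if re-testing does not depend on diagnosis. At the upper end it is large beside the 30% reduction used for sizing. For Gem no direction can be claimed. The documents cannot settle the size, but the linked records in uMkhanyakude can inform it, which makes a sensitivity analysis worthwhile. The planned primary estimate need not be replaced.

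**What to change.** Keep the survey-based rate ratio as the primary estimate. For uMkhanyakude, add:

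1. **A description.** Report survey re-testing by linked HIV-care status and calendar period. If re-testing does not differ by care status, the concern largely falls away.
2. **A weighted sensitivity analysis.** Weight each repeat-test interval by the inverse probability of being re-tested, estimated by period from age, residence and linked HIV-care status. Report the rate ratio with and without weights.
3. **A bounding analysis.** Count a linked treatment or laboratory record after a negative survey test as a seroconversion, with person-time for all resident women and one rule in every period. Use only the sources available since 2004, which precede every comparison period, and leave out the clinic-attendance capture that began in 2017. State that capture by treatment records itself rises with test-and-treat, so this is a bound and not a corrected estimate.

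Do the same in Gem only if linkage is confirmed for all periods; the article says only that it is possible there.

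The cost in uMkhanyakude is analysis work on records the article describes as linkable, plus somewhat wider intervals in the weighted analysis. No new data collection is needed there.

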#### Analysis of secondary outcomes

Secondary outcomes will be captured via the HDSS in the three surveillance sites (Table 2) as well as via the cohorts of young women in all four settings (Table 3). We will analyze population and individual level change, respectively, over time in these outcomes, using the calendar time periods described above for HIV incidence.

#### Analysis of causal pathways

To explore whether the hypothesized “mediators of change” lie on the causal pathway between the DREAMS interventions and HIV-related (secondary) outcomes (Table 2), longitudinal data collected from the nested AGYW cohorts at three time points over two years will be used (enrolment; 12 months; 24 months). The causal analysis will involve four main steps:Analysis of whether uptake of DREAMS interventions is related to an improvement in the “mediators of change”, between enrolment and follow-up at 12 and 24 monthsAnalysis of whether uptake of DREAMS interventions is related to “lower-risk” sexual behaviour, social protections, and biological protections, at follow-up at 12 and 24 monthsAnalysis of whether improved levels of the “mediators of change” are related to “lower-risk” sexual behavior, social protections, and biological protections, at enrolment and during follow-upCausal mediation analysis of the effect of DREAMS interventions on secondary outcomes (biological, behavioral, social), i.e., the extent to which any effect of DREAMS interventions on secondary outcomes after 12 and 24 months of follow-up is achieved through their effect on the “mediating” variables.

These analyses will adjust for important confounding variables measured at enrolment (for example, household socio-economic position) and an AGYW’s “propensity to receive” DREAMS interventions. This is because the criteria used by DREAMS implementing partners to select AGYW who will be invited to participate in the programme are also likely to influence the outcomes that are to be measured, i.e., they may be risk factors for HIV incidence and the secondary outcomes, and so may confound observed associations between uptake of interventions and these outcomes. For example, Implementing Partners are prioritising girls considered to have the highest risk of HIV infection (such as, those who are living in relatively poor households, are orphans, are out of school, or are young mothers, as identified via the ‘Girl Roster’ enumeration exercise and by community-based organisations) [19]. The characteristics that predict exposure to DREAMS will be identified using HDSS data, and the information across these characteristics will be synthesized into a single “propensity to be exposed to DREAMS” score (equivalent to an estimated probability of exposure to DREAMS, and taking values between 0 and 1), and AGYW will be categorized (stratified) into 4–5 groups on the basis of their propensity score. The association between uptake of DREAMs interventions and socio-economic and behavioural outcomes will be adjusted for the propensity score (in categories) as well as the individual characteristics that are the most important confounding variables.

#### Qualitative and process evaluation data

Analysis of the concurrent process evaluation data will follow the UK Medical Research Council guidance for process evaluation of complex interventions [18]. Data collected using the range of different methods, detailed above, will be carefully integrated to address the following process evaluation questions:How is delivery of DREAMS achieved and what is actually delivered? (Implementation)How does the delivered intervention produce change? (Mechanisms of impact)How does context affect implementation and outcomes? (Context)

The mechanisms to be scrutinised include increased demand for (awareness and acceptability), supply of (accessibility and availability), and adherence to (ongoing adoption) the interventions in the DREAMS core package, as per the HIV prevention cascade framework, to achieve coverage among the target populations [11].

#### Sample sizes

HIV incidence - the primary endpoint for the impact evaluation - will be measured using HDSS data in uMkhanyakude and Gem, and data from the cohorts of young women who sell sex in Zimbabwe. In uMkhanyakude, HIV incidence was ~ 6 per 100 person-years among AGYW aged 15–24 years old during 2011–2015, and ~ 4.6 and ~ 7.5 per 100 person-years among those aged 15–19 and 20–24 years respectively, based on a total of 7687 person-years of follow-up. Assuming, conservatively, that there will be ~ 3000 person-years of follow-up during 2017–2019 (40% of 7687), [20] then study power is > 90% to show an overall reduction in HIV incidence of 30, and > 90% in sub-group analysis of AGYW aged 15–19 and 20–24 years to show a 40% reduction in HIV incidence (Fig. 3a). In Gem, western Kenya, HIV incidence was ~ 0.7 per 100 person-years among AGYW aged 15–24 years during 2011–2016, based on a total of 8236 person-years of follow-up [21]. (Whereas sero-surveys are conducted annually in uMkhanyakude, they are less frequent in Gem: data are available from three sero-surveys in Gem between 2011 and 2016. Sero-conversions observed during this period, including those estimated from the 2016 survey, will be considered ‘pre-DREAMS’ because they are unlikely to be influenced by DREAMS by this early stage of implementation.) During 2017–2019, all AGYW in Gem will be sought for participation in the HDSS; with a participation rate of 70% in each year, and an annual out-migration rate of 20%, it is estimated that there will be ~ 9000 person-years of follow-up during 2016–2019. Study power is low to show a change in HIV incidence in sub-group analyses of AGYW aged 15–19 and 20–24 years, but ~ 80% to show an overall reduction of 45, and 90% to show an overall reduction of 50% in HIV incidence (Fig. 3b).

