#### Gem sub-county, Siaya county, Kenya

The Kenya Medical Research Institute (KEMRI)/Centers for Disease Control and Prevention (CDC) HDSS site in Siaya County of western Kenya covers a total population of approximately 223,000 people and 55,000 households, with demographic surveys three times a year. Siaya County includes three sub-counties: Rarieda, Siaya, and Gem. For the evaluation of DREAMS, the KEMRI/CDC platform in Gem will be used, as this is where HIV surveillance has been conducted most frequently and recently, i.e., three behavioral surveys and four rounds offering HIV testing services in 2011/2012, 2013/14, 2016, and 2017, among a random sample of one-quarter of all households and all resident members of those households as an open cohort [13].

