### Study design

The DREAMS package of interventions prioritises AGYW, but also includes ‘contextual’ components directed at young men, the families of AGYW, and the wider community (Table 1). Consequently, the overall impact of DREAMS interventions should be measured at community, or “population”, level. For example, if HIV incidence among AGYW is reduced following DREAMS interventions then this is likely to have been achieved through increased uptake of services and behaviour change among men as well as among AGYW themselves.

In the evaluation settings in which impact is measured in the general population (Nairobi, Gem, and Umkhanyakude), the primary way in which the impact of the DREAMS programme will be measured is through comparisons of HIV incidence (Gem and Umkhanyakude only), and HIV-related outcomes (in all 3 settings) across calendar time periods before, during early roll-out, and after DREAMS programmes have been established. This has the disadvantage that changes over time may be due to factors other than DREAMS interventions, but the advantage is that comparisons are made within the same setting and population, at multiple time points. A cluster-randomised trial design was not possible because the priority of the DREAMS Partnership was for rapid roll-out of DREAMS investments to geographic areas specifically chosen for their relatively high HIV prevalence, rather than to a randomly selected sample of areas [9].

For additional evidence of plausibility and impact, changes in outcomes will be assessed by estimating dose-response relationships between DREAMS uptake and outcomes at the small-area level [17]. ‘Layering’ of multiple interventions or services from the DREAMS core package, through integration and referrals, will be a key way of quantifying dose, for example, as the percentage of AGYW who received multiple intervention components and/or the minimum package designed for their age.

In Zimbabwe, the main way in which impact will be measured is through a comparison between 2 districts which will receive DREAMS interventions with 4 districts that will not. This alternative study design was chosen because the study population is young women who sell sex (not the general population of AGYW), who are at high risk of HIV acquisition in all 6 study districts, and a respondent-driven sample of YWSS will be enrolled into a cohort study and followed up for two years [8].

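### Gem: pre-DREAMS incidence comes from a random, repeatedly tested quarter of households and post-DREAMS incidence from all AGYW; this change in surveillance exposure is neither acknowledged nor separated from the before–after contrast

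*Protocol article*

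**What the plan says.** Under Study settings, Gem is chosen because HIV surveillance there was the most frequent and recent: "four rounds offering HIV testing services in 2011/2012, 2013/14, 2016, and 2017", carried out "among a random sample of one-quarter of all households and all resident members of those households as an open cohort".

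Under Sample sizes, the pre-DREAMS figure rests on three sero-surveys between 2011 and 2016: "HIV incidence was ~ 0.7 per 100 person-years among AGYW aged 15–24 years during 2011–2016", "based on a total of 8236 person-years of follow-up". For the later period, "During 2017–2019, all AGYW in Gem will be sought for participation in the HDSS". The expected yield is given as "it is estimated that there will be ~ 9000 person-years of follow-up during 2016–2019", "with a participation rate of 70% in each year, and an annual out-migration rate of 20" per cent.

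Under Study design, the article concedes that changes over time may have causes other than DREAMS. It gives as the compensating advantage that "comparisons are made within the same setting and population, at multiple time points". The analysis of the primary outcome then compares calendar periods using all available HDSS sero-survey data. No section mentions the move from a quarter sample to full coverage.

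**The concern.** The before–after design has no concurrent control in Gem, so its credibility depends on the two periods being observed alike. They are not observed alike in two respects.

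- **Testing history.** Before DREAMS, every resident of the sampled households, men included, was offered testing in 2011/12, 2013/14 and 2016. Afterwards, much of the person-time comes from households that were not part of that surveillance. The article itself treats testing as active prevention. HIV testing is in the core package (Table 1), and the Theory of change counts knowledge of status and ART uptake among male partners as a route to lower transmission.
- **Retest interval.** Directly observed incidence needs two tests on the same person. Pre-DREAMS rounds were roughly two years apart. The yearly participation rate suggests, without stating it, that later rounds are annual. A longer interval loses more of the mobile young women.

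Gem is one of only two general-population sites where the primary outcome is measured. A shift of moderate size there could hide part of a real benefit or imitate a small one.

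**Working it through.** **1. The plan's own power figure.** Inputs from Sample sizes: 0.7 per 100 person-years, 8236 person-years before and about 9000 after. Alpha is not stated; I assume two-sided 0.05.

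- Expected events before: 0.007 × 8236 = 57.7.
- Expected events after, 45% reduction: 0.007 × 0.55 × 9000 = 34.7. After, 50% reduction: 0.007 × 0.50 × 9000 = 31.5.
- Log rate ratio: power = Φ(−ln(RR)/√(1/e₀ + 1/e₁) − 1.96), which gives 0.794 for 45% and 0.879 for 50%.
- Rate difference, unpooled and pooled variance: 0.796 and 0.803 for 45%; 0.882 and 0.888 for 50%.

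The stated values (about 80% and 90%) reproduce to within about 2 points. They assume the same underlying rate in all households.

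**2. How much post-DREAMS person-time comes from added households.** The documents do not say, so I use a range.

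- Upper value: households contribute in proportion to number, so added households supply s = 0.75.
- Lower value: the quarter keeps its earlier yield. Taking 2011–2016 as five years, 8236/5 = 1647 person-years per year. Over three years that is about 4942, or 4942/9000 = 55% of the total, leaving s = 0.45.

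**3. Effect on the contrast.** Let r be the incidence in added households relative to the original quarter, apart from any DREAMS effect. The value of r is an assumption; r = 1 means no bias.

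Mix = (1 − s) + s·r. Apparent reduction = 1 − (1 − true reduction) × mix.

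| s | r | Mix | True 40% appears as | No effect appears as |
|---|---|---|---|---|
| 0.45 | 1.2 | 1.09 | 35% reduction | 9% increase |
| 0.75 | 1.2 | 1.15 | 31% reduction | 15% increase |
| 0.45 | 0.8 | 0.91 | 45% reduction | 9% reduction |
| 0.75 | 0.8 | 0.85 | 49% reduction | 15% reduction |

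With the log rate ratio formula, power for a true 45% reduction falls from 79% to 69% (s = 0.45) or 60% (s = 0.75) at r = 1.2. At r = 0.8, the chance of a falsely significant reduction rises from 2.5% to 7% or 13.5%.

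**4. Retest interval.** At 20% out-migration per year, 0.8² = 64% are still resident for a two-year retest, against 80% for a one-year retest. This applies a rate given for 2017–2019 to the earlier period and assumes annual later rounds. It shows a difference in who is observed, not a size of bias.

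**5. Cost of a like-for-like contrast.** Keep only original households after DREAMS, using the three formulas of step 1.

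| Post person-years | Power, 45% reduction | Power, 50% reduction |
|---|---|---|
| 2250 (25% of 9000) | 0.36–0.50 | 0.45–0.62 |
| 4942 (earlier yield, 3 years) | 0.62–0.69 | 0.72–0.80 |

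**6. Comparing original with added households in 2017–2019.** With 2250–4942 person-years in the original quarter, the rest of the 9000 in added households, and a 0–40% DREAMS reduction, the power to detect r = 0.8 or 1.2 at two-sided 5% is about 8–13%.

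**7. When the frame changed.** Study settings lists the 2017 round under the quarter sample. Sample sizes has all AGYW sought in 2017–2019, yet counts the 9000 person-years over 2016–2019. The date of the switch cannot be settled from these statements.

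**The case against.** The strongest reply is that the quarter was a random sample of all Gem households. A reader might infer from the change of frame that the two periods describe different populations. The documents do not support that: a random sample and a later full count target the same source population, so r = 1 is expected unless the surveillance itself changed risk or participation. This stands, and it limits the point to surveillance history and observation scheme.

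It is also fair that nothing in the article shows that offered testing lowered incidence in the quarter, or that other households lacked testing from other sources. The article refers to background scale-up of testing and treatment, and to wide roll-out of ART and VMMC in Gem before DREAMS. Prior testing would suggest r above 1. The r = 0.8 case runs against that mechanism and shows only the size of a shift in the other direction. The annual retest interval is likewise an inference.

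Finally, sensitivity analyses are often left to an analysis plan or site protocol, and neither is shown. The absence of such an analysis is therefore not itself an error. What remains is that the article states a design advantage which its own sampling description qualifies for Gem, and gives statements about timing that do not fit together.

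**Conclusion.** The point holds in limited form. In Gem the source population is the same in both periods, but exposure to surveillance testing differs and the retest interval probably does too. The article neither acknowledges this nor separates it from the effect of calendar period. Neither the direction nor the size of any shift can be derived from the documents. The illustrated range (a true 40% reduction appearing as 35–31%, or no effect appearing as a 9–15% reduction) rests wholly on the assumed r of 1.2 or 0.8 and on the assumed 45–75% share. The planned power calculation is not in error. The matter deserves a change because it touches the primary outcome at one of two general-population sites and the remedy is cheap.

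**What to change.** - **State when the frame changed** from the quarter sample to all AGYW, and reconcile the 2017 round, the 2017–2019 recruitment statement and the 2016–2019 person-years.
- **Flag households in the original sample.** As a pre-specified sensitivity analysis, report the before–after contrast within them beside the all-Gem estimate.
- **State the limits of that analysis.** Its power is about 0.36–0.69 for a 45% reduction, and it does not remove the effect of cumulative testing in those households.
- **Qualify the same-setting-and-population statement** under Study design for Gem: same source population, different surveillance history.
- **Present any 2017–2019 comparison of original with added households as descriptive only.** With 8–13% power, a null result would reassure no one.

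An all-Gem model with terms for period and household type is not worth adding. Added households have no pre-DREAMS data, so there are only three cells and the period effect simply returns the original-household contrast.

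The cost is a few sentences, one indicator that the surveillance records should already hold, and a secondary estimate with wide intervals. No new data collection is needed, and the all-Gem estimate remains the main one.
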